### Statistical tests

The primary outcome is neonatal bone mineral content as measured by DXA within two weeks following birth, presented as a continuous variable. The primary comparison is treatment (1000 iu cholecalciferol daily) versus control (placebo capsule daily). Linear regression modelling (ANOVA) will be used to describe the association of treatment on outcome. Student's t-tests may also be used to compare groups in secondary analyses.

### Ethical considerations

The study involves the participants undergoing various procedures with which they may not be familiar. Detailed information sheets are given to the participants and they have opportunities to discuss any concerns in detail with study personnel. The infant DXA assessments are associated with a low dose of radiation exposure equivalent to 2 days background radiation in Cornwall (UK) or 7 days in other parts of the UK. Data from the Princess Anne Cohort study showed a small excess of atopic asthma in children born to mothers with the highest levels of vitamin D in pregnancy [34]. However the numbers were lower than expected from the general population and confidence intervals wide. No associations between atopy in infancy and high levels of maternal vitamin D have been shown in the Southampton Women's Survey, and other studies have suggested neutral or negative associations [35-37]. The dose of vitamin D supplementation has been chosen to bring women just into the normal range, to avoid elevating it to supranormal levels.

### Reporting of adverse events

#### Anticipated Adverse Events

The development of some infrequent pregnancy-associated complications are anticipated to arise spontaneously during the study (ie cholestasis of pregnancy, pregnancy induced hypertension, gestational diabetes, pre-eclampsia, eclampsia, premature labour or delivery, instrumental delivery, caesarean section, miscarriage or stillbirth http://guidance.nice.org.uk/CG62/NICEGuidance/pdf/English).

#### Adverse drug reactions and adverse drug events

Any serious adverse event which is felt in any way to be related to the IMP is immediately reported (verbally or in writing) to the sponsor. This is followed by a detailed written report on the event. The local Principal Investigator decides whether to expedite reports of adverse events felt to be unrelated to the IMP. A record of all serious adverse events is kept in the trial master file regardless of whether reported within 24 hours to the sponsor.

The sponsor keeps detailed records of all adverse events relating to a clinical trial which are reported to them by the investigators for the trial. These records may be sent to the licensing authority if required.

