#### Suspected unexpected serious adverse reactions

The sponsor ensures that all relevant information about a suspected unexpected serious adverse reaction which occurs during the course of the trial and is fatal or life-threatening is reported as soon as possible to the MHRA, and the relevant ethics committee/data monitoring committee. This is done not later than seven days after the sponsor was first aware of the reaction. Any additional relevant information is sent within eight days of the report.

The sponsor ensures that a suspected unexpected serious adverse reaction which is not fatal or life-threatening is reported as soon as possible, and in any event not later than 15 days after the sponsor is first aware of the reaction, to the MHRA and the relevant ethics committee/data monitoring committee.

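### Prompt sponsor notification of a serious adverse event depends on its being judged related to the study drug; events judged unrelated, fatal ones included, have no stated deadline

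*Protocol article*

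**What the plan says.** The relevant rules are in three consecutive safety sections of the protocol article.

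- **Adverse drug reactions and adverse drug events.** A serious adverse event "felt in any way to be related to the IMP is immediately reported (verbally or in writing) to the sponsor", with a detailed written report to follow. For the remainder, "The local Principal Investigator decides whether to expedite reports of adverse events felt to be unrelated to the IMP". The section adds that "A record of all serious adverse events is kept in the trial master file regardless of whether reported within 24 hours to the sponsor". The sponsor's own file is described separately: "The sponsor keeps detailed records of all adverse events relating to a clinical trial which are reported to them by the investigators".
- **Anticipated Adverse Events.** Certain "infrequent pregnancy-associated complications are anticipated to arise spontaneously during the study". The list includes pre-eclampsia, eclampsia, premature labour or delivery, miscarriage and stillbirth.
- **Suspected unexpected serious adverse reactions.** For a fatal or life-threatening reaction, the sponsor reports to the regulator and to the ethics or data monitoring committee: "This is done not later than seven days after the sponsor was first aware of the reaction". For other such reactions the limit is 15 days, again counted from sponsor awareness.

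**The concern.** The sponsor is the body that must decide whether an event is a suspected unexpected reaction and report it onward. It can do so only for events it knows about. Under the printed rule, how soon it knows depends on whether someone at the site thinks the event is related to the study drug.

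That judgement is hardest where it matters most in this trial. A stillbirth or a case of eclampsia has many possible causes, the site is blinded to allocation, and a single case carries little information about a drug effect. If the site's view is mistaken, the correction should come from a second assessment by the sponsor. The printed rule lets that assessment be delayed without limit, even when the event is a death.

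The article itself accepts that events with no obvious link to the drug can be informative. Its section on the 18-21 week scan has fetal abnormalities recorded as adverse events because they may suggest new hypotheses about how vitamin D acts in pregnancy.

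**Working it through.** The point concerns a reporting rule. The plan has no figure to reproduce and no arithmetic applies beyond the planned recruitment of 2 × 600 = 1,200 mothers. The check is to follow one event through the text.

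1. **Event.** Take a stillbirth at any of the three centres. It meets the description of an anticipated complication, but the section listing those complications attaches no reporting rule to the list, so the general rule applies.
2. **Relatedness.** The study is double-blind, and under the randomisation section the code break envelopes are not available to the investigative team. Suppose the event is judged unrelated. The immediate route, which is triggered by suspected relatedness, does not apply. The wording is passive and does not say who makes this first judgement.
3. **Discretion.** The local Principal Investigator now decides whether to expedite. The section gives no criterion for that decision, no default, and no latest time for sending the report if it is not expedited.
4. **Record.** The event is entered in the trial master file. The text does not say when, or by when the sponsor looks at it.
5. **Sponsor's file.** The sponsor's detailed records cover what investigators have reported to it, so this event is absent from them until it is reported.
6. **Onward clocks.** The 7-day and 15-day limits run from sponsor awareness. Without awareness neither has started, and the sponsor has had no occasion to reconsider the causality opinion.

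Setting the two reporting steps side by side shows the gap:

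| Step | Depends on relatedness? | Faster for fatal or life-threatening events? | Time limit stated? |
|---|---|---|---|
| Site to sponsor, event thought related | Yes | No, all go immediately | Immediately |
| Site to sponsor, event thought unrelated | Yes | No | None |
| Sponsor to regulator and committee, suspected unexpected reaction | Yes | Yes | 7 or 15 days from awareness |

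The article distinguishes fatal and life-threatening events only after they have reached the sponsor. At the earlier step, where a site judges an event unrelated, it makes no such distinction.

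Geography adds to this. According to the section on regulatory aspects, the sponsor is a hospital trust in Southampton. Two of the three centres, Sheffield and Oxford, are elsewhere, so the sponsor's timely knowledge of events there depends on what the sites send.

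**The case against.** The strongest reply has several parts.

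- **Nothing is lost.** All serious adverse events are recorded, and the local discretion covers only whether to expedite. This stands. A reader might infer that events judged unrelated never reach the sponsor, and the text does not support that.
- **The threshold is broad.** Any suspicion of relatedness triggers immediate reporting. This narrows the group affected, but that group still has no deadline.
- **The list of complications is not an exemption.** This also stands. A reader might infer that listing stillbirth or pre-eclampsia as anticipated takes it out of reporting, or that sites will usually call such events unrelated. The article says neither. The point needs only that a site may do so.
- **Harms are captured by other routes.** Obstetric history is recorded at admission for labour, scan abnormalities are noted at 34 weeks, and pregnancy complications are collected from hospital notes at the neonatal DXA stage. These support a complete comparison of arms at the end. They do not give the sponsor timely notice of a single event.
- **Oversight may exist elsewhere.** The article is condensed, it refers to a data monitoring committee, and not all of its text after the safety sections was available. A reader might infer that the committee does not review serious events by arm. That cannot be concluded and is not claimed. The full protocol may also set a deadline. Even so, the article prints a rule of local discretion, and that rule can be judged as it stands.
- **The awareness-based clock is not itself an error.** Agreed. It matters here only because of the step before it.

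A reader might also see a conflict between immediate reporting and the reference to 24 hours. The two are compatible, and nothing rests on it.

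**Conclusion.** The concern holds in a limited form. As printed, prompt notification of the sponsor depends on a judgement that the event is related to the study drug. Expediting of all other events is left to each of three local Principal Investigators, with no stated deadline and no exception for fatal or life-threatening events or for fetal or neonatal deaths. The consequence is delayed sponsor awareness and a delayed second opinion on causality. Events do not disappear.

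The possible delay has no upper limit in the text, but its usual length and the number of events affected cannot be estimated. The article gives no rates of serious adverse events and does not say which listed complications would count as serious. A figure obtained by applying an assumed rate to 1,200 mothers would reflect only the assumption.

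The conclusion assumes that the article states the operating rule correctly. If the full protocol already sets a notification time for all serious adverse events, the article's wording should be brought into line with it and the point closes. Otherwise the change is worth making, because it concerns participant safety and costs little. The article describes the trial as ongoing, so the change can still take effect.

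**What to change.** Reword the section on adverse drug reactions and adverse drug events as follows.

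1. Every serious adverse event is notified to the sponsor within one fixed time, for example the 24 hours the section already mentions, regardless of the local opinion on causality. The local opinion is still recorded and sent with the report.
2. If workload is a concern, allow one explicit exception: complications on the anticipated list that are neither fatal nor life-threatening may go to the sponsor on a periodic listing at a stated interval.
3. Fatal or life-threatening events and fetal or neonatal deaths are always notified at once and never wait for the listing. Miscarriage and stillbirth are on the anticipated list, so the wording should say explicitly which route each follows.

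The trial master file record and the 7-day and 15-day limits can stay as they are. The cost is a protocol wording change and modest extra form handling by sites and sponsor, for events that the sites already record.

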#### Suspected unexpected serious adverse reactions

The sponsor ensures that all relevant information about a suspected unexpected serious adverse reaction which occurs during the course of the trial and is fatal or life-threatening is reported as soon as possible to the MHRA, and the relevant ethics committee/data monitoring committee. This is done not later than seven days after the sponsor was first aware of the reaction. Any additional relevant information is sent within eight days of the report.

The sponsor ensures that a suspected unexpected serious adverse reaction which is not fatal or life-threatening is reported as soon as possible, and in any event not later than 15 days after the sponsor is first aware of the reaction, to the MHRA and the relevant ethics committee/data monitoring committee.

### Regulatory Aspects

The study has received approval from MHRA, Southampton and Southwest Hampshire REC, University Hospital Southampton Trust R and D (Sponsor), UHS Data Protection Office. The IMP and placebos are manufactured in accordance with GMP regulations. The study is conducted in compliance with the Research Governance Framework for Health and Social Care, the Medicine for Human Use (Clinical Trials) Regulation 2004 and GCP. Indemnity has been provided through University Hospital Southampton NHS Foundation Trust (sponsor) and University of Southampton.

## Discussion and potential impact

As far as we know, MAVIDOS is one of the first ever tests, in humans, of the concept that an intervention in the mother during pregnancy may influence offspring bone mineral accrual. The result, positive or negative, should provide a step change in the evidence guiding current and future public health policy regarding vitamin D supplementation in pregnancy. The longer term follow up of these children will be important because it is possible that subtle effects of vitamin D supplementation, such as a reduction in allergy or asthma, will be only be detected after several years of observation. Given the current enthusiasm for vitamin D supplementation, and the possible widespread uptake, it is highly important that assessment of its effects is not limited purely to those during and immediately after pregnancy.

### Trial Status

The MAVIDOS study is ongoing.

## Abbreviations

Alb: Albumin; ALP: Alkaline phosphatise; ATP: Adenosine Tri-Phosphate; BA: Bone Area; BMC: Bone Mineral Content; BMD: Bone Mineral Density; BMUS: British Medical Ultrasound Society; BRU: Biomedical Research Unit; Ca: Calcium; COMA: Committee on Medical Aspects of Food and Nutrition Policy; DBP: Vitamin D Binding Protein; DEQAS: Vitamin D External Quality Assessment Scheme; DNA: Deoxyribonucleic Acid; DMC: Data Monitoring Committee; DXA: Dual-Energy X-ray Absorptiometry; GCP: Good Clinical Practice; GMP: Good Manufacturing Practice; GnRH: Gonadotrophin Releasing Hormone; HMSO: Her Majesty's Stationery Office; ISRCTN: International Clinical Trials Registry Number; IMP: Investigational Medicinal Product; IOV: Inter-operator Variation; IQ: Intelligence Quotient; ITT: Intention To Treat; LMP: Last Menstrual Period; MAVIDOS: Maternal Vitamin D Osteoporosis Study; MHRA: Medicines and Healthcare products Regulatory Agency; MRC: Medical Research Council; mRNA: messenger Ribonucleic Acid; NHS: National Health Service; NIHR: National Institute for Health Research; PTH: Parathyroid hormone; NICE: National Institute for Health and Clinical Excellence; SACN: Scientific Advisory Committee on Nutrition; SWS: Southampton Womens Survey; UK: United Kingdom; UHS: University Hospital Southampton NHS Foundation Trust; USA: United States of America; UVB: Ultra-violet B.

## Note

**Funding: Arthritis Research UK, Medical Research Council, Bupa Foundation and NIHR**. ISRCTN82927713, registered 2008 Apr 11. Date first participant randomised: 2008 Oct 7
